### Data analysis

Data will be transcribed verbatim, anonymised, and coding will be performed by at least two members of the research team. Codes will be developed based on RE-AIM and the programme theory. Analysis will be based on the elements of RE-AIM and the programme theory and will be coded for both inductive (emergent themes) and deductive (data driven themes). We will examine divergence and similarities across the contact centres to develop a comprehensive understanding of how the theories of change operate across a range of contact centres and also assess the mechanisms of change, implementation, sustainability and potential for a larger effectiveness study.

## Development of a health economic study (aim 3)

The health economic component of the study (Research question 8) will aim to lay the ground work for a health economic component of any future definitive trial, from a) an NHS and PSS perspective (Following the NICE reference case [75], and b) an employer’s perspective (which may be important at an implementation stage to leverage commercial support). With regards to a), while it is possible that fitness level improvement may be observable within a trial, it is not anticipated that such fitness would be likely to translate into changes in “hard” health outcomes or patterns of healthcare utilisation (ie primary or secondary care utilisation) within an observable trial period, hence standard within trial analysis is not appropriate. Instead the health economic component of the study will focus on scoping the possibility for future economic modelling of longer term outcomes through consultations with managers and clinicians regarding possible model structures and associated data sources, with targeted literature searches for potential parameter sources where identified. If appropriate this may be extended to include employer perspective outcomes. Within trial observations will be limited to estimates of the cost of direct implementation costs (such as workstation adjustments, information sessions or similar) presented alongside descriptive statistics regarding the utilisation of each, and measures of workplace productivity reported. The latter will be determined through consultation with local management to identify measures most useful to the participating sites, though it is anticipated that these will include most of those outlined in Table 3.

| **Outcome** | **Measure** |
| --- | --- |
| Absenteeism | WHO HPQ absenteeism and presenteeism questions |
| Presenteeism | WHO HPQ absenteeism and presenteeism questions |
| Productivity | Could include (depending on the contact centre): call handling time, time spent talking, time spent on hold, time spent wrapping up a call . |
| Quality of Life | EQ-5D |

## Progression criteria

We will proceed to a future larger study if all of the following are satisfied:

1. 95% confidence intervals for the primary outcome includes a clinically relevant reduction in sedentary time of 45 minutes per day or greater in favour of the intervention. This would reflect substantial progression towards accumulating recommended quantity of 2h/day standing/light activity during working hours [54] for employees in predominantly desk-based occupations.
2. Intervention successfully delivered in at least five of the sites within the study period, if at least one person in each site was able to use/experience at least one activity.
3. At least 10% of employees at a site were able to use/experience at least one of the intervention activities in the sites at which the intervention was successfully delivered.
4. Out of all the participants using/experiencing at least one of the intervention activities, primary and secondary outcome data was collected in at least 75% of participants overall.
5. Contamination between sites is low or else it is envisaged that contamination can be addressed in the study design of a future study.
6. It is envisaged that any practical difficulties in delivering the intervention across multiple sites or in measuring effectiveness can be overcome when conducting a future large-scale study.

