Whilst there continues to be debate over the design and its limitations (e.g. [59]), some of which are valid, evaluations of public health interventions often have to be pragmatic and take into account the stakeholders and context of the intervention involved (in this instance the contact centres). We argue that we need a pragmatic option for a number of reasons. First, it could potentially cause delays in the evaluation process if we waited until all contact centres were at the same stage of readiness for implementation. A structural/location/organisation change in one contact centre could delay the process. Second, it would be more costly and resource intensive to implement the intervention and collect baselines data in all the contact centres at a single time point. We have requested two researchers, but due to the spread of locations in Scotland and North East England, this would make implementation and data collection difficult and increase the potential for failure. Third, contact centres are already wanting to implement the intervention when they hear about it. It is unlikely to cause any harm. It has been implemented in one contact centre for over a year and only positive benefits have been reported. Journals such as The Lancet Global Health and Trials are publishing the results of such designs [e.g. 60, 61].

Setting

Ten contact centres with more than 100 employees in Scotland and/or the North East of England. These two areas have the highest rates of contact centres in the UK, employing up to 6% of the workforce in these regions [62]. We will consider other areas of England if there is interest and to ensure we have 10 contact centres taking part.

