## Study population

As this is a cluster RCT, contact centres rather than the staff employed in the contact centres (including managers, supervisors and call handlers) will be recruited. All staff will have the opportunity to participate in the intervention. For the evaluation components, staff will have the option of taking part on an opt-in basis.

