## Sampling and sample size

All employees at a site are likely to take part in some or all of the intervention activities. However, employees will have the option of taking part in the research evaluation component. When we discuss the sample size, we are referring to the number of people taking part in the research evaluation (not those only taking part in intervention activities). The sample size and target difference are the same as another similar study that proposed a sample size of 160 per arm to detect a reduction in workplace sedentary behaviour of 45 minutes per day [49]. Since we will have 6 control and post-intervention cross-sectional comparisons (see **Figure 1**), the target sample size is 160/6=~27 per contact centre per data collection period. There are 10 contact centres so we aim to recruit at least 270 employees in total taking part in the research evaluation. An aim of this feasibility study is to test sample size assumptions and produce a more accurate sample size calculation for a future study.

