### Data collection timepoints

In order to minimise cost and participant burden for this trial, and since the main purpose of the trial is to test study processes and procedures, data will only be collected at a maximum of three occasions per site: at the end of the control period, and at 3 and 6 months after the end of the intervention in each site. Sites 1 and 6 will not have a control period, and sites 5 and 10 will not have a post-intervention period, in order to minimise the duration of the study for which there is no concurrent vertical comparison between control and post-intervention periods. To increase the response rate, participants will be paid a small amount (£5 end of control period and £10 for 3 months data) for taking part in data collection.

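### Progression criterion 4 counts outcome-data completeness only among activity users, so it can be met with less than 75% completeness in the sample that is analysed

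*Protocol*

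**What the plan says.** The protocol's Progression criteria section makes the decision conjunctive: "We will proceed to a future larger study if all of the following are satisfied". Criterion 4 is the completeness rule: "Out of all the participants using/experiencing at least one of the intervention activities, primary and secondary outcome data was collected in at least 75" per cent, taken over all sites together. The section does not define participants and does not say which data collection occasion has to be complete. Criterion 3 is the reach rule, with a floor and no ceiling: "At least 10% of employees at a site were able to use/experience at least one of the intervention activities".

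Elsewhere the protocol keeps two groups apart. Under Study population, "All staff will have the opportunity to participate in the intervention", while the evaluation is opt-in. Sampling and sample size expects that employees generally will join in activities, but says of the sample size that "we are referring to the number of people taking part in the research evaluation (not those only taking part in intervention activities". In the same section "the target sample size is 160/6=~27 per contact centre per data collection period", giving at least 270 in total.

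The Statistical analysis section fits its model to the observed data from every participant. Research question 3 for Aim 2 asks for recruitment and loss to follow-up, with staff turnover as the example.

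**The concern.** The completeness rule should describe the sample that a confirmatory trial would measure and analyse. That sample is the consented evaluation participants, whatever they did with the activities. Criterion 4 instead selects on having used an activity, which is likely to favour people who are engaged and still employed. Someone who consents and never tries an activity, or who leaves before trying one, counts neither as a success nor as a failure.

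The rule could therefore be met while completeness in the analysed sample is below 75%. The decision to proceed would then rest on a retention figure that is too favourable, and the size of a future trial could be planned on it.

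**Working it through.** **Inputs**
- Threshold of 75%, pooled over sites (Progression criteria).
- 160 per arm, 6 comparisons, 10 centres, at least 270 evaluated (Sampling and sample size).
- Centres of more than 100 employees (Setting).
- Annual turnover of 24% (Retention) or 21% (the section on contact centres as a setting).
- Control wait of 3 to 12 months (Control/comparator group).
- Share of evaluation participants who use an activity, *u*: not given, so a range is shown.

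**1. The plan's own figure.** 160/6 = 26.67, rounded up to 27; 27 × 10 = 270. Both agree with the protocol.

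**2. Full-sample requirement.** 0.75 × 270 = 202.5, so 203 people with data.

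**3. Natural reading: evaluation participants who used an activity.** Users = 270*u*. The number needed is 0.75 × 270*u*, rounded up. The last column is the lowest overall completeness at which the criterion is still met, reached if no non-user has data.

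| *u* | Users | Needed | Needed/270 |
|---|---|---|---|
| 100% | 270 | 203 | 75% |
| 90% | 243 | 183 | 68% |
| 50% | 135 | 102 | 38% |
| 10% | 27 | 21 | 8% |

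More generally, if a fraction *r* of the non-users have data, overall completeness at a bare pass is 0.75*u* + *r*(1 − *u*). This is below 75% whenever *r* is below 75%. With *r* = 50% (an assumption), it is 0.675 + 0.050 = 72.5% at *u* = 90%, and 0.375 + 0.250 = 62.5% at *u* = 50%.

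**4. Leaving before first use.** With a constant leaving rate, the fraction gone after *m* months is 1 − (1 − *a*)^(*m*/12). For *a* = 21% to 24%, this is 6% to 7% over 3 months and 21% to 24% over 12 months. These figures apply to people who consent at the start of their site's wait. For those who consent near its end, the loss before first use is smaller.

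**5. Secondary reading: all staff who used an activity.** With 270 evaluated, the pooled criterion can be met only if total users do not exceed 270/0.75 = 360. Ten centres of more than 100 staff have more than 1,000 staff, so the pooled uptake limit is below 360/1,000 = 36%. At full uptake, completeness would be below 270/1,000 = 27%.

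**The case against.** The strongest reply has four parts.

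- **Wording.** Criterion 3 counts employees and criterion 4 counts participants, a word the protocol mostly uses for people in the research. This stands, and it makes the natural reading the main one.
- **Uptake.** The protocol expects nearly all staff to take part in some activity. If 90% or more of evaluation participants do so, the minimum is 68% or higher, close to the intended 75%. This also stands: the low-use rows of the table are possibilities, not forecasts. But the protocol does not state the share, and its own reach criterion accepts 10% of employees.
- **Other provisions.** Loss to follow-up is a research question, turnover is recorded, missing data get sensitivity analyses, and criterion 6 asks whether difficulties in measuring effectiveness can be overcome. None of these sets a completeness threshold, so they soften the problem without removing it.
- **Nature of the rule.** Criterion 4 is a descriptive proportion, so selecting on use after randomisation does not bias an effect estimate. That is correct. The objection here is only that the proportion describes the wrong group.

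A reader might also infer that criterion 4 ignores control-period data, or that it cannot be met because "sites 5 and 10 will not have a post-intervention period". The text supports neither. It names no occasion, so control data from people who later use an activity are not excluded, and it does not state that post-intervention data are required. People who leave after using an activity also stay in the denominator.

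**Conclusion.** The denominator of criterion 4 is wrongly specified for a mandatory decision rule, and the occasion is left open. The rule can be met with fewer than the 203 of 270 that full-sample completeness would need: down to 183 (68%) at 90% use and 102 (38%) at 50% use. These minima assume the planned 270 and no data from non-users. Given the uptake that the protocol expects, the real shortfall may be modest. This should be fixed, but it does not invalidate the design.

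A reader might go further and conclude that high uptake makes the criterion impossible to meet, that each centre has a ceiling on users, or that criteria 3 and 4 contradict each other. The protocol does not support these as the main point. They depend on the secondary reading, in which participants means all activity users. Even then the criterion is pooled, so a centre with high uptake can be offset by others. The limit of about 360 users is also soft, because 270 is a minimum. What can be said is that the secondary reading would conflict with the near-universal uptake expected in "Ten contact centres with more than 100 employees". That is a further reason to define the term.

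**What to change.** Restate criterion 4 as follows: primary outcome data obtained from at least 75% overall of consented evaluation participants scheduled for a data collection occasion at their site (as set out under Data collection timepoints), regardless of activity use, with leavers counted as missing unless followed up. Report completeness separately for control and post-intervention occasions, and report secondary-outcome completeness on the same denominator.

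The change is short and needs no new data, but it has costs:
- The measured rate will probably be lower than among activity users only, so the sponsor should confirm that 75% is still the intended threshold. As a guide, with 21% to 24% annual turnover, 16% to 19% of staff leave within 9 months (1 − 0.79^0.75 and 1 − 0.76^0.75). The 9 months cover an intervention of about 3 months and the 6-month follow-up. Turnover alone would leave 81% to 84%.
- Because staff leave and join, and the target of 27 applies per data collection period, the protocol must say who counts as scheduled at each occasion.
- Secondary outcomes would be reported but no longer part of the threshold.
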